### **3. Study Methods**

#### ***Trial Design***

The trial design is described in detail in previously published study protocol ([name] et al., 2021) and briefly described here.

The study is a randomised, placebo controlled, double blinded, intervention study in which participants were grouped into two different arms. One arm received protein food supplement plus prebiotic food supplement and the other arm received protein food supplement plus placebo (maltodextrin). Supplements were posted to participants in pre-mixed identical sachets, which they were advised to take daily for 12 weeks, in a glass of water or other drink. Participants in both groups were also advised to undertake resistance exercises. All participants had a study visit carried out via video teleconferencing software at the beginning and end of the study. They also completed questionnaires, food diaries and cognitive testing remotely at the beginning and end of the study. Lastly the participants also collected biological samples (urine, stool, saliva, and capillary blood) and posted these to the department at the beginning and end of the study. A subset of participants also completed an additional study visit in-person at the department for validation measures.

Randomisation was used to control for equal distribution of key characteristics that may confound between group comparisons. Participants were randomised as twin pairs, with one twin from the pair in the prebiotic food supplement arm and one twin from the pair in the placebo arm. Twin pairs are matched for age and often for sex, early environment, baseline genetic sequence, socioeconomic status etc., proving a strong model for detecting changes while adjusting for both observed and unobserved confounding.

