### ***d. Overall Improvement***

In addition to analysing the primary and secondary outcomes by arm, group-wide comparisons will be carried out for the following variables of interest: weight, BMI, SPPB

score, balance score, grip strength, chair rise time, gait speed, IPAQ MET minutes/week, IPAQ score, SNAQ score, CANTAB cognitive test results and serum metabolites.

Paired tests will be carried out to assess for differences between baseline and study end point, two sample t-tests for continuous variables (normally distributed), Mann-Whitney test for non-normally distributed continuous variables, and Pearson's chi-squared tests for categorical variables.

While there is no control group for these analyses, these will tell us whether the protein and exercise intervention that all twins will receive was beneficial for the aforementioned variables of interest, irrespective of gut microbiome modulation with a prebiotic food supplement. This analysis will also be repeated using two subgroups of interest, protein intake at baseline, and frailty index at baseline.

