### ***c. Safety Outcomes***

All safety outcomes will be reviewed, collated, and reported where relevant. These include adverse events, serious adverse events (SAEs), hospitalisations or other significant medical events.

Adverse effects will be defined as present or absent (coded 1 and 0 respectively) for each participant. Participants who dropped out prior to receiving any of the intervention will be excluded. Each binary safety outcome will be analysed by treatment group using a chi-square test or Fisher exact test. The likelihood of an SAE being associated with the study intervention will be rated as none, unlikely, possible, or probable. Frequencies and percentages of any adverse events in each study arm will be calculated.

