#### ***i. Food diary data***

The food diary data will be presented in tables, by sex. Paired tests will be carried out to assess for differences between baseline and study end point, two sample t-tests for continuous variables (normally distributed), and Mann-Whitney test for non-normally distributed continuous variables.

Over and under reporting will be assessed using the Goldberg energy intake to BMR (basal metabolic rate) ratio method . BMR will be calculated using the revised Harris-Benedict equation , and multiplied by an adjustment factor for physical activity . A ratio of this adjusted BMR to energy intake (kcal/day) will be generated. Over and under reporters will be identified as those who are two standard deviations above or below this ratio. If over an/or under reporters are identified, an additional dietary table will be presented, with these participants excluded.

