### ***b. Main Analyses***

Paired tests will be carried out to assess for differences between each arm at baseline; two sample t-tests for continuous variables (normally distributed), Mann-Whitney test for non-normally distributed continuous variables, and Pearson's chi-squared tests for categorical variables.

All primary statistical analyses will be unadjusted. Subsequent analyses carried out will be adjusted for relevant covariates which are known or suspected *a priori* to be associated with the outcome, as described henceforth. Stata and RStudio will be used for all statistical analysis.

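### Three SAP sections call for paired tests but name independent-sample tests, and the pooled before-after change is read as a protein-and-exercise effect

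*Combined protocol and SAP*

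**What the plan says.** Three sections of the SAP use the same construction.

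- **5.4 Overall Improvement** (headed d. under section 5), baseline versus study end: "Paired tests will be carried out to assess for differences between baseline and study end point, two sample t-tests for continuous variables (normally distributed". For other variable types it continues: "Mann-Whitney test for non-normally distributed continuous variables, and Pearson's chi-squared tests for categorical variables".
- **Section 7, Food diary data**, baseline versus study end, again announced as paired: "two sample t-tests for continuous variables (normally distributed), and Mann-Whitney test for non-normally distributed continuous variables".
- **7.2 Main Analyses**, arm versus arm at baseline: "Paired tests will be carried out to assess for differences between each arm at baseline; two sample t-tests for continuous variables (normally distributed", with Mann-Whitney and Pearson chi-squared for the other variable types.

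The arms are matched by design. Under Trial Design, pairs are randomised "with one twin from the pair in the prebiotic food supplement arm and one twin from the pair in the placebo arm".

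Section 5.4 then interprets the pooled before-after comparisons: "these will tell us whether the protein and exercise intervention that all twins will receive was beneficial", irrespective of the prebiotic. The same sentence opens by conceding that these analyses have no control group.

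**The concern.** The two halves of each instruction conflict. A programmer who follows the word paired will run one set of tests; one who follows the named tests will run another. Two-sample t, Mann-Whitney and Pearson chi-squared all treat the two sets of values as independent. Baseline versus end is the same person twice, and arm versus arm is co-twin versus co-twin. The named tests ignore that correlation, so their standard errors are wrong. With positive correlation, real change is harder to detect.

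The second problem is interpretation. A pooled change cannot isolate protein and exercise: every participant received protein and exercise advice, half also received the prebiotic, and nothing controls for elapsed time or for repeating the CANTAB and physical tests. Admitting that there is no control group and then saying that the comparison shows benefit leaves the conclusion at odds with the caveat.

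**Working it through.** **No figure to reproduce.** None of the three sections states a sample size, power or test-specific error rate. The check is what the named tests would do to data with this structure.

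**Inputs.** There are 72 participants (Supplementary Tables), taken as all measured twice. Alpha is 0.05 (SAP, Descriptive Statistics; two-sided is my assumption). The SD of log10 chair-rise time is 0.126 (SAP, Sample size calculation), assumed equal at both visits. Within-person correlation ρ is not given; I show 0.3, 0.5 and 0.7.

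**Type I error of the two-sample t on paired data.** The true variance of the mean difference is 2σ²(1−ρ)/n, but the two-sample test uses 2σ²/n. It therefore rejects when the true z exceeds 1.96/√(1−ρ), and the error rate is 2[1 − Φ(1.96/√(1−ρ))].

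| ρ | 1.96/√(1−ρ) | Formula | Simulated, two-sample t | Simulated, paired t |
|---|---|---|---|---|
| 0.3 | 2.34 | 0.019 | 0.0197 | 0.051 |
| 0.5 | 2.77 | 0.0056 | 0.0060 | 0.050 |
| 0.7 | 3.58 | 0.00035 | 0.00015 | 0.047 |

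(Simulation: 20,000 runs, 72 pairs.) Pearson chi-squared on paired binary data behaves in the same way: with an assumed prevalence of 20% and correlation 0.5 or 0.7, simulated type I error is about 0.007 or 0.001.

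**Power.** A 10% fall is −log10(0.9) = 0.0458. The standard error used by the two-sample test is 0.126 × √(2/72) = 0.0210; the true one is 0.0210 × √(1−ρ) = 0.0176, 0.0148 or 0.0115. Two-sample power is 1 − Φ((1.96 × 0.0210 − 0.0458)/true SE); paired power is 1 − Φ(1.96 − 0.0458/true SE). The other falls are treated alike.

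| Fall in chair-rise time | Two-sample (ρ = 0.3 / 0.5 / 0.7) | Paired (ρ = 0.3 / 0.5 / 0.7) |
|---|---|---|
| 5% | 14 / 10 / 5% | 24 / 32 / 49% |
| 10% | 60 / 62 / 66% | 74 / 87 / 98% |
| 20% | all above 99% | all above 99% |

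**Which test was run for diet?** Table S4 reports p = 0.021 for energy and 0.032 for fat, labelled paired. Missing counts of 13 and 24 leave n = 72 − 13 = 59 at baseline and 72 − 24 = 48 at the end. A Welch two-sample t from the printed means and SDs gives:

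- Energy: (1569.5 − 1476.0)/√(397.7²/59 + 438.7²/48) = 93.5/81.8 = 1.14, p = 0.26.
- Fat: (66.1 − 62.7)/√(21.6²/59 + 22.1²/48) = 3.4/4.25 = 0.80, p = 0.43.

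The reported values are not two-sample results. They fit a paired t with within-person correlation of roughly 0.8 to 0.9 (if 40 to 48 people have both diaries).

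**A paired test is not enough for the pooled group.** Treating 72 changes as independent ignores that they come in twin pairs. If changes correlate within pairs with coefficient ICC (assumed), the error rate of the pooled paired test is 2[1 − Φ(1.96/√(1+ICC))] = 0.062, 0.086 or 0.110 for ICC = 0.1, 0.3 or 0.5. This error runs the other way, towards false positives.

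**What the pooled change estimates.** Let c be the change with protein, exercise advice, time and retesting, and e the added prebiotic effect. With equal arms the pooled mean is ½(c + e) + ½c = c + e/2. It carries half of any prebiotic effect, and c is itself not the effect of protein and exercise alone.

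**The case against.** The best defence is that the governing word is paired and the named tests are loose drafting. The footnotes to Tables S4 to S6 report paired t-tests, and the Table S4 check supports that for before-after diet. This largely stands, and it limits the practical damage. It does not cure the SAP text. Nor is labelling consistent: Table S6's footnote also claims a paired test for arm versus arm, yet the baseline weight p-value of 0.28 matches a two-sample t (71.8 (14.0) versus 75.8 (17.2), 36 per arm: 0.283). One row is an indication, not proof.

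A reader might infer from energy and fat that the named tests would always have given much larger p-values. The tables do not support that. The printed means come from everyone with data at each visit, while a paired test uses only people with both, so the contrast mixes test and sample. These are also two of the larger gaps. Oligosaccharide goes the other way: 0.039 by two-sample t (0.014 to 0.097 allowing for rounding) against 0.329 reported.

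A reader might also extend the point to 6.3 Safety Outcomes, which says: "Each binary safety outcome will be analysed by treatment group using a chi-square test or Fisher exact test". That section never calls for paired tests, so it does not contradict itself, and a matched test is not reliably better there. Assume from Table S2 that 8 participants were affected in arm 1 and 2 in arm 2, with 36 per arm. Fisher gives p = 0.085; exact McNemar gives 0.109, 0.070 or 0.031 with 0, 1 or 2 concordant pairs, a number that the documents do not give.

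On interpretation, the SAP does state that there is no control group, and the planned table of group-wide comparisons has a neutral title. The fault is confined to the sentence that draws the conclusion.

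**Conclusion.** The point holds for 5.4, the food diary section and 7.2: the named tests contradict the word paired and do not fit the data structure. With positive correlation they are conservative, costing power and not creating false positives. The sizes above rest on an assumed correlation of 0.3 to 0.7, equal SDs at both visits and complete data on 72 people. For a fall as large as 20% the choice of test hardly matters.

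It would be too strong to say that the reported before-after diet p-values are wrong, or that the trial's main comparison is compromised. The former appear to come from paired tests; the latter is a mixed model with twin pair as a random effect. These are supportive analyses, so the correction is worth making but is not critical.

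The causal reading in 5.4 is unsupported whichever test is used.

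**What to change.** **Tests.** For baseline versus end in 5.4 and the food diary section, name the paired t-test, Wilcoxon signed-rank and, for categorical variables, McNemar. McNemar covers two categories only; the IPAQ category has three planned levels, so add a marginal homogeneity test. Preferably, use a mixed model with person and twin-pair random effects for the pooled analyses, because simple paired tests ignore twin clustering. For any arm-versus-arm baseline comparison in 7.2, use the tests matched on twin pair. Leave 6.3 as it is on this point.

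**Interpretation.** In 5.4, keep the caveat about the missing control group. Replace the claim about benefit with a statement that the analysis describes change over 12 weeks pooled across arms, and that this change cannot be attributed to protein and exercise, because half the sample took the prebiotic and time and retest effects are uncontrolled. Placebo-arm change may be shown alongside as description. It removes the prebiotic from the estimate but is still uncontrolled.

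**Cost.** A few lines of SAP wording and no new data. The placebo-arm display has half the sample.

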| Vitamin B12 µg/d             | 3.5 (1.9)      | 4.4 (2.3)      | 3.7 (2.0)      |  | 2.9 (1.6)      | 2.6 (1.3)      | 0.026* |
| Folate µg/d                  | 222.1 (82.9)   | 212.5 (77.3)   | 220.0 (81.2)   |  | 183.8 (77.1)   | 212.8 (99.9)   | 0.079  |
| Vitamin C µg/d               | 91.4 (73.9)    | 61.9 (26.1)    | 84.9 (67.3)    |  | 69.9 (47.3)    | 72.4 (43.5)    | 0.084  |
| Vitamin D µg/d               | 3.5 (3.8)      | 2.9 (1.9)      | 3.3 (3.4)      |  | 2.7 (2.3)      | 2.1 (2.8)      | 0.200  |
| 25-Hydroxy D3 µg/d           | 0.0 (0.1)      | 0.0 (0.0)      | 0.0 (0.1)      |  | 0.4 (1.2)      | 0.0 (0.2)      | 0.092  |
| Vitamin D3 µg/d              | 0.3 (0.6)      | 0.6 (0.9)      | 0.4 (0.7)      |  | 0.3 (0.7)      | 0.3 (0.8)      | 0.228  |
| Vitamin E µg/d               | 8.0 (3.3)      | 8.9 (5.8)      | 8.2 (3.9)      |  | 6.2 (2.6)      | 8.2 (5.1)      | 0.014* |
| Vitamin K1 µg/d              | 78.3 (89.5)    | 54.7 (37.4)    | 73.1 (81.3)    |  | 50.2 (37.8)    | 49.1 (53.5)    | 0.442  |
| Food groups and other |                |                |                |  |                |                |        |
| Vegetables g/d               | 160 (120)      | 107 (63)       | 149 (112)      |  | 141 (64)       | 95 (61)        | 0.469  |
| Fruits g/d                   | 143.5 (104.2)  | 148.9 (107.7)  | 144.7 (104.0)  |  | 141.2 (141.5)  | 143.1 (92.2)   | 0.167  |
| Alcohol g/d                  | 9.7 (15.6)     | 18.6 (21.3)    | 11.6 (17.2)    |  | 7.7 (8.7)      | 13.5 (19.8)    | 0.063  |
| Water g/d                    | 1931.3 (625.8) | 2075.4 (840.2) | 1963.0 (673.4) |  | 1858.9 (622.3) | 1848.2 (782.2) | 0.124  |
| Missing Data (n)             | 10             | 3              | 13             |  | 20             | 4              | 24     |

All data presented as mean (standard deviation). Please note the nutritional intake from the intervention sachet is not included in these dietary data. NSP: non-starch polysaccharides. AOAC fibre comprises of the total amount of non-digestible polysaccharides, and includes e.g., lignin and resistant starches, measured with a set of methods developed by the Association of Analytical Chemists (AOAC). \* Denotes significance.

P values are within group comparisons of the total population between baseline and end of intervention performed using a two-sided paired t-test

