| Cognition       | Scores for 5 main tests | continuous | mean,(SD) |

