## **7. Statistical Analysis**

### ***a. Descriptive Statistics***

All outcomes will be presented using descriptive statistics; normally distributed data by the mean and standard deviation (SD) and skewed distributions by the median and interquartile range (IQR). Binary and categorical variables will be presented using counts and percentages. P values of  $\leq 0.05$  will be considered sufficient to reject the null hypothesis.

Outliers will be assessed by examining plots and checked for possible erroneous entry. Where necessary, results with and without outliers will be compared to assess for discrepancies in the results, and this will be discussed if found to be discrepant.

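### SAP 5.4 rests a benefit conclusion on many before-after tests, repeated in two subgroup sets, each at P≤0.05 with no multiplicity rule

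*Combined protocol and SAP*

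**What the plan says.** SAP section 5, item d (Overall Improvement, cross-referenced as Section 5.4) plans baseline-to-end comparisons over the whole trial population. The list starts with weight, BMI and SPPB and continues "score, balance score, grip strength, chair rise time, gait speed, IPAQ MET minutes/week, IPAQ score, SNAQ score, CANTAB cognitive test results and serum metabolites". Table 1 of the SAP describes the cognition entry as "Scores for 5 main tests".

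The section acknowledges that there is no control group, but says "these will tell us whether the protein and exercise intervention that all twins will receive was beneficial" for these variables. It then extends the exercise: "This analysis will also be repeated using two subgroups of interest, protein intake at baseline, and frailty index at baseline". No cut-points or number of levels are given for either subgroup variable.

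On significance, SAP section 7, item a (Descriptive Statistics) says that P values of 0.05 or less "will be considered sufficient to reject the null hypothesis". That sentence is not limited to any one analysis, and the SAP gives no other threshold. Section 5.4 contains no hierarchy, correction or exploratory label.

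Multiplicity is addressed elsewhere. SAP 7.2.2 adjusts the serum metabolite analysis, in a paragraph about differences between the arms using the mixed model of 7.2.1. The microbiome subsection of 7.2.2 adjusts its models, and Supplementary Note 1 applies Benjamini-Hochberg (BH) at a false discovery rate of 10%. Protocol 17.2 adjusts the mixed-model association analyses and the microbiome models.

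**The concern.** The section attaches a conclusion about benefit to a collection of tests and does not say how many must succeed, which ones count, or at what joint error rate. As written, one P value at or below 0.05 among the whole-group tests, the subgroup repeats or the metabolites would support a statement that the protein and exercise programme helped. The more tests there are, the less such a statement means.

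The plan accepts the principle for its other large families, so this is a gap in coverage and not a considered choice that the SAP explains. The issue is the error rate of the family. It is separate from whether an uncontrolled before-after change can be read causally, and it does not touch the randomised comparison.

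**Working it through.** The documents state no family-wise error rate for these tests, so there is no figure of the plan's own to reproduce.

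**Count of tests**
- Single measures in SAP 5.4: weight, BMI, SPPB, balance, grip strength, chair rise time, gait speed, IPAQ MET minutes, IPAQ score, SNAQ = 10.
- CANTAB: 5 scores (SAP Table 1).
- Total without metabolites: 10 + 5 = 15. It would be 16 if the six CANTAB variables of Supplementary Note 2 were used.
- Subgroup repeats: levels not given. Assuming two levels for each of two variables, there are 1 + 4 = 5 passes, so 5 × 15 = 75 tests. If each repeat were a single extra pass, 3 × 15 = 45.
- Metabolites: number not given.

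**Expected false positives if every null is true** (m × 0.05, valid under any correlation)
- 15 tests: 0.75 (16 tests: 0.80)
- 45 tests: 2.25
- 75 tests: 3.75
- Metabolites: 100 × 0.05 = 5 per 100 tested, per pass

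**Chance of at least one, 15 tests**
- Independent: 1 − 0.95^15 = 0.54.
- By simulation with a common correlation between outcomes (assumed): 0.36 at 0.5 and 0.14 at 0.9.

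The outcomes overlap (weight with BMI, SPPB with its components, the two IPAQ measures), so 0.54 is an upper value.

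**Chance of at least one, 75 tests**

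The 75 tests cannot be treated as one block with a single correlation. Each half is part of the whole sample, and the two halves of one variable share no participants. I therefore simulated four equal cells (protein half × frailty half), each with its own 15 correlated statistics. The whole-group statistic is the sum of the four cells divided by 2. Each half's statistic is the sum of its two cells divided by √2.

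| Correlation between outcomes (assumed) | 15 tests | 75 tests, nested |
|---|---|---|
| 0 | 0.54 | 0.94 |
| 0.5 | 0.36 | 0.79 |
| 0.9 | 0.14 | 0.41 |

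**Secondary check: the dietary table**

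SAP 7.1(i) plans similar tests for the food diaries: "Paired tests will be carried out to assess for differences between baseline and study end point". Supplementary Table S4 reports them: "P values are within group comparisons of the total population between baseline and end of intervention performed using a two-sided paired t-test". It has 35 rows (11 + 7 + 13 + 4). Vitamin A carries no P value, which leaves 34 tests and 34 × 0.05 = 1.7 expected false positives. Four are starred: vitamin E 0.014, energy 0.021, vitamin B12 0.026 and fat 0.032. The BH ratios P × 34 / rank are:
- 0.014 × 34 / 1 = 0.476
- 0.021 × 34 / 2 = 0.357
- 0.026 × 34 / 3 = 0.295
- 0.032 × 34 / 4 = 0.272

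The smallest BH-adjusted value over all 34 is 0.272, so none passes at 5% or 10%. Against that, the probability of four or more hits among 34 independent true nulls is 0.088.

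**The case against.** The best defence is that section 5.4 lies outside the Hypothesis Testing section, whose formal null hypotheses are all between arms. The section concedes the lack of a control group. The subgroup section says the study is not powered for its analyses, in the same paragraph that assigns protein intake and frailty index to the group-wide comparisons. The sponsor could add that silence is not a refusal to adjust, and that the metabolite sentence in 7.2.2 was meant to cover the before-after metabolites too. All of this limits the reach of the point. None of it supplies an error rate for a section that promises a verdict on benefit, and the 7.2.2 sentence as written concerns the arms.

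Three stronger readings are tempting, and the documents do not support them.
- A reader might infer that chance hits are to be expected even among the 15 outcomes tested once. The expected number is 0.75, and at correlation 0.5 no false hit is the likelier result. An expectation above one needs the subgroup repeats or a sizeable metabolite panel.
- A reader might infer that the metabolites make false hits certain. That needs a panel size, which is not given.
- A reader might infer that the starred dietary changes are false, or that the dietary plan shares the fault in full. Failing BH means not confirmed, and a probability of 0.088 does not show that chance produced them. The food-diary plan sits under Descriptive Statistics ("The food diary data will be presented in tables, by sex"), with no benefit language and no subgroup repeat, and no text in the documents asserts falls in intake. If those tables serve to detect drift in background diet, strict adjustment would also make drift harder to see.

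**Conclusion.** The point holds for SAP 5.4. A benefit conclusion is tied to at least 15 tests plus metabolites, repeated in two subgroup sets, at an unadjusted 0.05. For the 15 outcomes once, the inflation is moderate: a 0.36 chance of a false finding (0.14 to 0.54) in place of 0.05. With the repeats it is large: about 0.79 (0.41 to 0.94), with 3.75 expected false positives. These figures assume that all nulls are true, five CANTAB scores, a common correlation between outcomes, and two equal halves per subgroup variable; the last two are my assumptions. The expected counts do not depend on the correlation.

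The dietary tables are a side note: their stars are unadjusted and none survives BH, which does not make the changes unreal. The randomised primary and secondary comparisons are not affected. The change should be made because the text supports an inflated claim and the remedy is cheap.

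**What to change.** In SAP 5.4:
1. Apply BH within two families, the clinical and CANTAB outcomes and the before-after metabolites, at a level stated in advance. The 10% used for the microbiota is the documents' own precedent; if another level is chosen, say why. If all nulls are true, BH at level q also holds the chance of any rejection to q when tests are independent or positively dependent.
2. Base any statement about benefit on the adjusted values.
3. Report the protein-intake and frailty repeats as exploratory estimates with 95% confidence intervals and no significance statement, and give the cut-points.
4. Replace the promise of a verdict on benefit with exploratory wording.
5. Say whether the metabolite adjustment in 7.2.2 was meant to cover the before-after tests.

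For the dietary tables, a footnote that P values and stars are unadjusted is enough.

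The cost is a few sentences and one column of adjusted P values, with no new data. The downside is that some nominally significant changes lose their star.
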